### Blinding

Due to the nature of the intervention, neither GPs nor patients can be blinded. For practical reasons, study personnel cannot be blinded either. However, all analyses will be conducted by a blinded statistician.

### Intervention

The intervention consists of the arriba-PPI tool applied during a regular or extra patient contact in the GP practice. Before the intervention, study personnel will visit the intervention group practices to provide training for GPs and practice nurses that comprises the use of PPIs in general, the SDM processes, the withdrawal of drugs, and how to use the arriba-PPI tool. GPs are supposed to use the arriba-PPI tool with their participating study patients for the following six months and, subsequently, the arriba-PPI tool application shall be used for all patients with a PPI prescription for another six months.

The application of the arriba-PPI tool requires the installation of the arriba software on one or several computers of the GP practice to enter relevant patient data including name, gender, PPI substance, dose, and indication. Once patient data are entered, a choice of four sections is available represented by the following buttons: traffic light; weighing scale; procedure; information; and print.

The decision aid is displayed as a traffic light system to clarify whether stopping PPIs is recommended or not. Green indicates the clear recommendation for a withdrawal, yellow indicates that withdrawal usually is recommended, and red indicates that withdrawal usually is not recommended. The weighing scale provides arguments for and against withdrawal (such as long-term harm, short-term complaints, social constraints). GPs are supposed to discuss with their patient the pros and cons for taking PPIs, taking the patient’s preferences into consideration. Depending on the decision made by the patient and GP, the software provides suggestions for next steps to take, in particular the measures to be taken when complaints arise during withdrawal. Finally, the patient will get an individualized printout covering information on long-term effects of the drug, a withdrawal plan with dosing steps, follow-up appointments, and so on.

### Control

GP practices participating in the control group of the study will provide care as usual for 12 months. GP practices will not make any extra appointments with their patients for this study.

### Measurements

The primary endpoint is the cumulated DDDs of PPIs per study patient at six months (T1). Secondary endpoints are the proportion of PPI patients in the practice during the six months after allocation (T1), the cumulated DDDs of PPIs per study patient during the 12 months after allocation (T2), the proportion of PPI patients in a practice during the time span of 6–12 months after allocation (T2), and the average accumulated total DDDs of PPIs in a practice for all patients during the time span of 6–12 months after allocation (T2).

For outcome measurement, information on PPI prescription (substance, dose, package size) per patient will be recorded from the practice software for a time span of six months before T0 to 12-month follow-up. Furthermore, the number of all patients taking PPIs per practice and the number of patients per practice will be assessed for the time span of T0 to 12 months after allocation (Fig. 2).

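### Practice-wide counts start only at T0, so the two proportion endpoints cannot be adjusted for their own baseline; the baseline and data source of the practice DDD endpoint are left unclear

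*Protocol article*

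**What the plan says.** The Measurements section of the protocol article lists three practice-level secondary endpoints:

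- "the proportion of PPI patients in the practice during the six months after allocation (T1");
- "the proportion of PPI patients in a practice during the time span of 6–12 months after allocation (T2");
- "the average accumulated total DDDs of PPIs in a practice for all patients during the time span of 6–12 months after allocation (T2").

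Two collection windows follow. Prescription details (substance, dose, package size) "per patient will be recorded from the practice software for a time span of six months before T0 to 12-month follow-up". By contrast, the count of PPI patients and "the number of patients per practice will be assessed for the time span of T0 to 12 months after allocation".

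Under Intervention, use of the tool is staged. First, "GPs are supposed to use the arriba-PPI tool with their participating study patients for the following six months"; after that, "the arriba-PPI tool application shall be used for all patients with a PPI prescription for another six months".

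Under Data management and statistical analysis, secondary outcomes go into multilevel models that may carry patient-level or cluster-level covariates. Under Randomization, the only stratification factor is study center.

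**The concern.** Both proportions are built from two counts, PPI patients and all patients, and both counts begin at T0. A pre-T0 value of the outcome is usually the most useful covariate for a practice-level comparison, and here it is not collected, although the same practice software is already searched for the preceding six months. Months 0–6 cannot serve as a baseline for the T2 proportion, because they follow allocation and GP training. An analysis plan cannot repair this later if the data were never extracted.

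The practice-wide T2 endpoints matter because the stated secondary objective is effectiveness of implementation in months 6–12, when the tool is meant for every PPI patient. Practices are likely to differ in prior prescribing: an open invitation is combined with an insurer's mailing to practices above its median prescribing rate (Recruitment of GP practices and patients), and randomization does not balance on prescribing level. At stake are wide confidence intervals and chance imbalance that the analysis could not correct for.

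**Working it through.** **1. The windows side by side**

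| Item | Stated window | Needed for |
|---|---|---|
| Prescription details per patient | 6 months before T0 to 12 months | DDD endpoints |
| Number of PPI patients in the practice | T0 to 12 months | numerator of both proportions |
| Number of all patients in the practice | T0 to 12 months | denominator of both proportions |

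The prescription row can be read in two ways.

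- *Study patients only.* The practice DDD endpoint then has no baseline, and no source is named for all-patient DDDs, since only counts are listed for all patients. In favor of this reading: if every PPI patient's prescriptions were extracted, the number of PPI patients would follow from them, and a separate count with a later start would be unnecessary.
- *All PPI patients.* Practice DDDs then have a six-month baseline. In favor: the section names study patients explicitly when it means them, and the outcomes being served include all-patient DDDs.

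The text does not settle this. Under either reading the denominator of the proportions has no stated pre-T0 window, so the gap for the two proportions remains.

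**2. The plan's own sample size, as a check on its inputs** (Sample size calculation)

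- CV: 7850.89 / 8244.47 = 0.952. Mean per patient: 8244.47 / 56.20 = 146.7. Effect: 15% of 146.7 = 22.
- Patients per arm before clustering: 2 × [139.7 × (1.960 + 0.842) / 22]² = 633.
- Design effect: 1 + (15 − 1) × 0.1 = 2.4, giving 1519 patients per arm.
- 1519 / 15 = 101.3, rounded up to 102 practices per arm, or 204. The stated figure is reproduced.

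This calculation concerns the primary endpoint and is not affected by the point made here.

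**3. Illustration for practice total DDDs only**

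Inputs: CV 0.95 (one insurer, quarterly practice totals); 210 practices, taken as 105 per arm; two-sided 5%. The baseline correlation r is an assumption; the documents give none.

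- Relative SE without baseline: 0.95 × √(2/105) = 0.131.
- Detectable difference at 80% power: (1.960 + 0.842) × 0.131 = 36.7% of the mean.
- Power for 15%: Φ(0.15/0.131 − 1.96) = 0.21.
- Half-width of the 95% CI: 1.96 × 0.131 = about 26% of the mean.
- With a baseline covariate the SE is multiplied by √(1 − r²):

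| Assumed r | Detectable difference | Power for 15% |
|---|---|---|
| none | 36.7% | 0.21 |
| 0.7 | 26.2% | 0.36 |
| 0.8 | 22.0% | 0.48 |
| 0.9 | 16.0% | 0.75 |

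No such table can be made for the proportions, because the documents give no variance for them.

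**4. Share of PPI patients for whom the tool is intended in months 0–6**

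Study patients number 15 to 25 per practice. One insurer alone averages 56.20 PPI patients per practice. The share is therefore at most about 15/56.2 = 27% to 25/56.2 = 44%, and lower once other insurers' patients are counted.

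**The case against.** Several stronger readings are tempting, and the documents do not support them.

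- *The practice-level endpoints must be compared unadjusted.* Not so. Cluster-level covariates are planned, study center is known, and GP demographics are collected before randomization. What is missing is the outcome's own baseline, which these do not replace.
- *All three endpoints lack any pre-T0 data.* This is not established for practice DDDs, because the prescription extraction may cover all PPI patients. T0 is also not defined in the visible text, and the schedule figure is not shown.
- *The 37% and 21% describe all practice-level endpoints.* They rest on the spread of one insurer's quarterly totals. The proportions already divide by practice size. Even for the DDD endpoint the CV could differ over six months and all insurers, and would be smaller if the average is meant per patient.
- *A 15% effect shrinks to 0.44 × 15% = under 7% in the T1 proportion.* This mixes units. The 15% is a fall in DDDs, and a dose reduction leaves the count of users unchanged.
- *The T1 proportion should be demoted to descriptive.* That is a preference. The text states intended use, GPs and nurses are trained on PPIs in general, and a learning effect is expected, so spill-over is a legitimate target.

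It is also fair to say that only the primary endpoint was powered, so low power on a secondary endpoint contradicts nothing. Even at r = 0.9 the detectable difference is 16%, so a baseline improves the DDD comparison without bringing it to 80% power for 15%. None of this answers the missing pre-T0 window for the counts.

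**Conclusion.** The point holds in a limited form. As written, the two practice-level proportions cannot be adjusted for their own baseline. Whether the same is true of practice DDDs depends on a sentence that can be read either way; on the narrower reading that endpoint also lacks a stated data source.

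Because practices are randomized, the consequence is lost precision and exposure to chance imbalance, not bias. The primary endpoint keeps its pre-T0 data. The only available measure of size is illustrative and applies to practice DDDs alone: power for 15% of about 21% without a baseline against 36–75% with one. It assumes that the one-insurer CV carries over, that arms are equal, and that r lies between 0.7 and 0.9. The loss for the proportions cannot be quantified from the documents.

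Separately, any effect on the T1 practice-wide proportion will be diluted, since in months 0–6 the tool is intended for well under half of a practice's PPI patients. That is a caution for interpretation, not an error.

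**What to change.** 1. Start the practice-wide extraction of both counts (PPI patients and all patients) six months before T0, matching the prescription data.
2. State that PPI DDDs for all patients are extracted over the same window, and say whether the existing prescription extraction covers study patients or all PPI patients.
3. Adjust each practice-level endpoint for its baseline value and study center.
4. When reporting the T1 practice-wide proportion, note that the tool was then intended only for the 15–25 study patients per practice.

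The cost is a slightly larger query per practice in records that are already being searched for that period, plus a few lines in the protocol and analysis plan. The sample size and primary analysis do not change.

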**Fig. 2 Fig2:**
[figure not shown]
Schedule of enrolment, interventions, and assessments for the arriba-PPI trial according to SPIRIT

To evaluate the real utilization of the arriba-PPI tool and to control for confounding, GPs from the intervention group will fill out a case report form for each patient after consultation with the arriba-PPI tool, which provides information on the original indication, the result of the consultation, and on medication changes. At T1, GPs will be asked whether there has been a change in the PPI medication for each individual study patient and, if so, why. Additionally, after T1 study centers will call all patients for a short-structured phone interview based on mainly closed questions to gain information about the current PPI medications and other medications for gastric problems they are taking to monitor medication shifts, e.g. into self-medication (over-the-counter medication). In the intervention group, patients will also be asked whether the arriba-PPI tool was used during consultations.

Finally, demographic data from all participating GPs will be collected before randomization using a written questionnaire.

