### Recruitment of GP practices and patients

Before the recruitment of GP practices and patients, recruitment-regions will be selected. In these prespecified regions, all GPs will be informed about the study and will be invited to participate. All GP practices will obtain a written invitation (letter and/or fax) and will be followed up by phone calls. The study design will be presented at several network meetings for GPs, where the GPs will be asked to participate. Additionally, the health insurance BARMER will identify GP practices with a higher prescription rate of PPIs compared to the median prescription rate of all practices of the BAMER database. BARMER will contact these practices twice via mail and invite them to participate.

Participating GP practices will be visited by a research assistant from the study center providing detailed information about the study before patient recruitment. GP practices will then invite all consecutive patients with a PPI prescription consulting the practice to participate in the study and will inform them about the study orally and in writing. After completing recruitment, the practice will be randomized.

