### Data management and statistical analysis

Data will be recorded into SPSS at each study center and transferred to the blinded trial statistician. We will use intention-to-treat and per-protocol analyses. The primary outcome will be analyzed by multilevel analyses with the statistical program R following intention-to-treat principles [31]. These analyses take into account the clustering of patients by practices and allow for different modelling of predictors, e.g. group affiliation as fixed and/or random effect. Furthermore, these analyses allow adjustment for variables which showed differences between the intervention and control groups despite randomization and which are considered to be of prognostic importance. In case of missing variables, suitable imputation methods will be used [32]. We will perform sensitivity analyses (worst case, best case, complete case) in order to check for the influence of missing data on the results.

The evaluation for the secondary outcomes will also be done by multilevel analyses by adopting covariates on patient and/or cluster level. Elaborated evaluations in multivariate procedures allow a more detailed analysis of prescription behavior. All statistical tests will be two-tailed and an alpha of 5% will be used throughout. Besides statistical significance, effect sizes will also be evaluated [33].

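### A form completed only in the intervention arm, after the tool consultation, is assigned to control confounding, which it cannot do

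*Protocol article*

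**What the plan says.** In the protocol article, the Measurements section (text after Fig. 2) introduces the form as a way to judge actual use of the tool "and to control for confounding, GPs from the intervention group will fill out a case report form for each patient after consultation" with the tool. It is a form "which provides information on the original indication, the result of the consultation, and on medication changes".

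Four other places bear on this:

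- Recruitment of GP practices and patients fixes the order of events: "After completing recruitment, the practice will be randomized". The tool reaches only practices allocated to it, so every form is filled in after allocation.
- Control describes usual care, and "GP practices will not make any extra appointments with their patients for this study". No counterpart of the form is mentioned.
- Measurements says that "information on PPI prescription (substance, dose, package size) per patient will be recorded from the practice software", from six months before T0 to the 12-month follow-up. No arm restriction is stated, and indication is not in the list.
- Data management and statistical analysis states: "The primary outcome will be analyzed by multilevel analyses with the statistical program R following intention-to-treat principles". It then allows "adjustment for variables which showed differences between the intervention and control groups despite randomization", provided they are thought prognostic.

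**The concern.** Confounding of an arm comparison is handled with variables that are measured in both arms and not affected by treatment. The form fails on both counts. It exists in one arm, and within that arm only where the tool consultation took place. Two of its items record what the intervention led to. The third, original indication, is a legitimate baseline characteristic, but an unblinded GP records it after allocation.

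Two things are at stake. The stated purpose cannot be achieved. An analyst who takes the sentence at face value and puts form items into a between-arm model, or uses the form to filter the intervention arm for a per-protocol set, would bias a comparison that randomization had made fair.

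**Working it through.** **1. What is available, when and in which arm (protocol article)**

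| Item | Arms | Timing | Usable to adjust the arm contrast? |
|---|---|---|---|
| Original indication (form) | intervention, consulted patients only | after allocation | no |
| Consultation result (form) | same | after allocation, effect of the intervention | no |
| Medication changes (form) | same | after allocation, on the path to cumulated DDDs | no |
| Indication entered into the tool (Intervention section) | intervention only | after allocation | no |
| GP question at T1 on medication change and reason | no restriction stated | after allocation | no |
| Prescriptions in the six months before T0 | no restriction stated | before allocation | yes |
| GP demographics | all GPs | before randomization | yes |

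**2. What happens if form items are entered anyway**

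The value would be absent for every control patient. Complete-case fitting drops the whole control arm, so no arm effect can be estimated. Imputation would rest entirely on the relation seen in consulted intervention patients. Coding controls as a constant allows a fit but biases it, as step 4 shows.

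**3. The plan's own figures**

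The target difference is 0.15 × 146.7 = 22.0 DDD, as stated. With SD 139.7, two-sided alpha 0.05 and 80% power, 633 patients per arm are needed. The design effect is 1 + 14 × 0.1 = 2.4, and 633 × 2.4 / 15 = 101.28. That rounds up to 102 practices per arm, 204 in total, as stated. The present point does not touch this number; 22 DDD serves only as the scale below.

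**4. Illustration of the direction of bias**

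Assumptions that are *not* in the document: 40% of patients have a clear indication, worth +40 DDD; 80% of intervention patients have a form; the whole effect of −22 DDD acts through a recorded reduction. The chance of a reduction at consultation is 0.15 with and 0.55 without the indication (scenario A), or 0.30 in both groups (scenario B).

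- Share of the intervention arm reducing: A, 0.8 × (0.4 × 0.15 + 0.6 × 0.55) = 0.312; B, 0.8 × 0.30 = 0.24.
- DDD drop per reducer: A, 22 / 0.312 = 70.5; B, 22 / 0.24 = 91.7.

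When a binary covariate is zero throughout the control arm, the arm coefficient is the mean of intervention patients coded zero minus the mean of all controls.

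*Adjusting for the form's medication change.* Intervention patients without a reduction are compared with all controls. In A their share with the indication is 0.4 × (1 − 0.8 × 0.15) / (1 − 0.312) = 0.352 / 0.688 = 0.512, so the coefficient is 40 × (0.512 − 0.4) = +4.5. In B the share stays at 0.4 and the coefficient is 0. The true effect has vanished.

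*Adjusting for indication known only from the form, otherwise coded zero.* A share of 1 − 0.8 × 0.4 = 0.68 of the intervention arm is coded zero. Among them 0.2 × 0.4 / 0.68 = 0.118 truly have the indication, which contributes 40 × (0.118 − 0.4) = −11.3. The reducers contribute:

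- A: −(0.8 × 0.6 × 0.55 / 0.68) × 70.5 = −0.388 × 70.5 = −27.4; total −38.7.
- B: −(0.8 × 0.6 × 0.30 / 0.68) × 91.7 = −0.212 × 91.7 = −19.4; total −30.7.

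A simulation under the same assumptions (1,000 trials, 204 practices × 15, ICC 0.1, least-squares estimates, simulation error about 0.26) agrees:

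| Model | A | B |
|---|---|---|
| Unadjusted | −22.0 | −22.2 |
| Indication measured in both arms | −22.1 | −22.2 |
| Form's medication change | +4.4 | −0.2 |
| Form-only indication | −38.7 | −31.0 |

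**The case against.** The strongest reply is that nothing in the analysis section uses the form. The primary analysis is an intention-to-treat multilevel model, its endpoint comes from practice software, and the adjustment rule covers variables that differ between arms, which a one-arm variable cannot be shown to do. Patients are also enrolled before allocation, so only chance imbalance is left to correct, and pre-T0 prescriptions can serve for that. All of this stands. It limits the consequence but does not rescue the sentence in Measurements, which gives the form a purpose it cannot serve.

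A reader might infer more than the article supports:

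- *That the primary result is biased.* It is not, provided form items stay out of the model. The figures in step 4 rest on invented parameters and on a coding of controls that the article never proposes. They show direction, not expected size.
- *That indication is missing for every control patient.* The text describes no such collection, but this is a condensed article and the assessment schedule in Fig. 2 is not shown.
- *That the form is the only source of indication.* The Intervention section has indication entered into the tool as well. That too is confined to intervention practices, so it does not help adjustment.
- *That the per-protocol set is built on the form.* The article does not define that set, and intervention patients are also asked by phone whether the tool was used.
- *That a planned analysis by indication is lost.* No objective or endpoint calls for one.

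**Conclusion.** The point holds in a limited form. The article states a purpose, control of confounding, that a single-arm, post-allocation, consultation-dependent form cannot fulfil. Two of its three items are consequences of the intervention and should not be conditioned on. This follows from who completes the form and when, and needs no numerical assumption.

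The consequence is conditional. With form items left out, the primary comparison is unaffected and the sample size of 204 practices is unchanged. With them included, bias could run in either direction and, under the assumptions shown, could be as large as the 22 DDD target itself. Whether control practices record indication elsewhere cannot be settled from the text. Severity is minor to moderate. The form remains sound for describing tool use within the intervention arm.

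**What to change.** 1. In Measurements, delete the confounding purpose and describe the form as documentation of tool use within the intervention arm.
2. State that form items will not enter any between-arm model, and will not define a per-protocol set that filters the intervention arm while leaving the control arm whole.
3. If adjustment or subgrouping by indication is wanted, take it as documented before allocation from the practice records of all study patients in both arms. Use one procedure, during the prescription extraction that is already planned. Do not obtain it by asking GPs at T1: they are unblinded, and intervention GPs will by then have been trained and will have entered indications into the tool, so the arms could classify differently.
4. If indication is not pursued, adjust for the pre-T0 prescription data already being collected.

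Items 1 and 2 change wording only, and item 4 needs no new data. Item 3 adds a little extraction work per patient, and indication may be incompletely documented in the records.
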